## Introduction

### Background

The treatment of ulcerative colitis (UC) patients with moderate to severe inflammatory activity with anti-tumor necrosis factor alpha (TNFα) antibodies leads to a clinical remission rate of 10% (ULTRA1 study, 80/40 mg adalimumab) [1] to 39% (ACT1 study, infliximab 5 mg/kg body weight [2] and SUCCESS study [3]) after 8 weeks of therapy. However, it must be taken into account that patient selection in clinical trials clearly influences both response and remission rates. In addition, the results of these studies are not consistent with those of observational trials with a high degree of target population representativeness. International guidelines therefore recommend that the success of an anti-TNFα therapy beyond the 12-week mark must be predicted as soon as possible in order to adjust or discontinue treatment depending on the clinical situation [1,4-6]. An unsatisfactory response to anti-TNFα medication after Week 12 often leads to a discontinuation of treatment. The early prediction of clinical response could therefore help to optimize therapy and potentially avoid ineffective treatments [7].

In this regard, the PURSUIT study showed that the administration of the new human anti-TNFα immunoglobulin G1 monoclonal antibody golimumab to subjects with moderately to severely active UC induced clinical response in Week 6 after two injections (Weeks 0 and 2) in 51.0-54.9% of patients in a randomized clinical trial, whereas placebo response was 30.3% (*P*<.001) [8].

After 6 weeks, responders in the golimumab group were randomized again to receive either placebo or 50 or 100 mg golimumab doses every 4 weeks for a further 54 weeks. The analysis of clinical response in this trial showed a statistically significant response for golimumab 50 mg versus placebo (*P*<.001) after 54 weeks (47.0% and 31.2% respectively) [9].

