### Statistics

#### Analysis

Our aim is to study the detection of a positive trough level of golimumab of >2.5 μg/ml and a significant reduction in fecal calprotectin of 50% from baseline in Week 6 as a reliable predictor for clinical response in Week 26 during long-term treatment with golimumab. In this connection, a level between 2.5 μg/ml and 4.3 μg/ml is regarded as being associated with a therapeutic effect of golimumab [8,9].

Statistical analysis is mainly carried out with descriptive methods such as frequency tables, and statistical parameters such as mean, standard deviation, and quantiles. Bar graphs are used for qualitative data and box-and-whisker plots for quantitative data. In addition, inferential statistical analysis is carried out with relevant significance tests and confidence intervals. Missing data are not imputed.

In order to evaluate the primary outcome, the test problem presented in the section on statistical hypotheses is formulated and solved. The test is carried out with a power of 80% and a two-tailed significance level of alpha=.05. Analysis is carried out with a logistic regression model based on the percentage change of fecal calprotectin and golimumab trough levels. In addition, secondary parameters (eg, ATGs, CRP, WBC) are also analyzed to identify further correlations between the data of Week 6 and therapy outcome in Week 26. The aim is to identify further constraints to the statistical model in order to take into account all relevant parameters in the final version of the algorithm. Secondary outcomes are assessed in an explorative way, that is, no pre-formulated hypotheses are tested. The *P* values obtained are thus interpreted according to Fisher’s method: a *P* value is considered a metric value, and the smaller the *P* value, the larger the significance of the corresponding effect. No interim analyses are planned. Data analysis is carried out only once, at the end of the study.

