### Sample Size

#### Rationale

Sample size is planned based on data from studies researching a correlation between fecal calprotectin and response to an anti-TNFα therapy.

De Vos et al [10] describe response rates as: “After 10 weeks anti-TNFα therapy induced endoscopic remission in 63% (confidence interval: 47–78%) of patients”. Molander et al [11] describe the correlation between the predictive quality of fecal calprotectin and the remission rate. The results are displayed in Table 1.

**Table 1 table1:** Cross classification of fecal calprotectin predictive quality and remission.

		Fecal calprotectin decline		Total
		Yes	No	
Remission				
	Yes	30	3	33
	No	6	21	27
Total		36	24	60

Based on these results, the odds ratio (OR) is calculated as OR (30*21) / (6*3)=35. It should be noted that for the above study the cut-off point for fecal calprotectin decline was a reduction of >75% from baseline. Lower cut-off points, for example, a 50% reduction, would lead to smaller OR, as the number of patients with neither decline nor response is described as being almost constant in the above-mentioned literature: “Absence of decrease in calprotectin levels at week 6 identified patients resistant to the treatment” [11]. It is therefore assumed for sample size calculation that 80% of the patients will have a “fecal calprotectin decline.” Table 2 summarizes the scenarios that have been taken into consideration.

**Table 2 table2:** Sample size rationale: Response rates and their effect on resulting OR for 9 different scenarios.

Scenario	Response rate (%)	OR
1	40	10
2	40	20
3	40	30
4	50	10
5	50	20
6	50	30
7	60	10
8	60	20
9	60	30

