#### Calculation

Sample size calculation is carried out with the statistical analysis software SAS. Table 3 shows the required number of evaluable patients for each scenario. It is expected that 5% of the intention-to-treat principle population will be excluded. Sample size is inversely proportional to the OR and the response rate.

**Table 3 table3:** Sample size calculation: Number of evaluable subject and total number of subjects considering dropouts for 9 different scenarios.

Scenario	Response rate, %	OR	Evaluable subjects, n	Subjects including potential dropouts, total n
1	40	10	58	61
2	40	20	40	42
3	40	30	34	36
4	50	10	50	53
5	50	20	34	36
6	50	30	29	31
7	60	10	45	48
8	60	20	31	33
9	60	30	26	28

To prevent study failure due to an underpowered study, a worst case scenario with a response rate of 40% and an OR of 10 is used as a basis for sample size. A total of 58 evaluable subjects are therefore necessary for the trial, thus 61 patients must be recruited.

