### Study Population

The evaluation of primary and secondary outcomes is carried out according to the intention-to-treat principle. The corresponding population comprises all patients included in the study regardless of possible protocol violations (eg, dropouts). In addition to intention-to-treat analysis, sensitivity analysis according to the per-protocol principle is carried out. Relevant protocol violations leading to exclusion from the per-protocol group are defined in the statistical analysis plan.

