#### End of Patient Participation

The observation of each patient ends according to the schedule with the last study visit. A patient’s participation in the study will be terminated prematurely if at least one of the following criteria is met: (1) withdrawal of informed consent, (2) termination of golimumab treatment, (3) lack of medical justification for further participation in the study, (4) premature termination of the complete trial, or (5) subsequent discovery that not all inclusion criteria are met and/or that any exclusion criteria are met.

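### Patients who stop golimumab before Week 26 leave the primary model with no outcome, and if they are mainly non-responders the predicted response probabilities are too high

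*Protocol article*

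**What the plan says.** All references are to the protocol article.

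- **End of Patient Participation** lists the events that end participation early. One is "2) termination of golimumab treatment".
- **Statistics, Analysis** states "Missing data are not imputed". The primary analysis is a logistic regression of Week 26 response on Week 6 calprotectin change and golimumab trough level.
- **Study Population** says the intention-to-treat population "comprises all patients included in the study regardless of possible protocol violations (eg, dropouts".
- **Background** says "An unsatisfactory response to anti-TNFα medication after Week 12 often leads to a discontinuation of treatment".
- **Sample Size, Calculation** says "It is expected that 5% of the intention-to-treat principle population will be excluded", which takes 58 evaluable patients to 61 recruited.

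No section says how a patient who stopped golimumab counts at Week 26.

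**The concern.** Once participation has ended, no Week 26 partial Mayo score is due. Without imputation or an outcome rule, the logistic model cannot use that patient. The intention-to-treat set keeps the patient in name, but the model fitted to it does not.

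The timing makes this more than a loss of numbers. By the Background's account, stopping for poor response tends to come after Week 12, which lies between the Week 6 predictors and the Week 26 outcome. The patients removed are then likely to be mainly treatment failures.

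The study aims to give, at Week 6, the probability of response at Week 26, so that ineffective treatment can be recognised early. Complete-case probabilities apply to patients still on the drug at Week 26, and nobody knows at Week 6 who those will be.

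**Working it through.** **Inputs from the document.** "The test is carried out with a power of 80% and a two-tailed significance level of alpha=.05". For the sample size, "a worst case scenario with a response rate of 40% and an OR of 10 is used as a basis for sample size", and it is "assumed for sample size calculation that 80% of the patients will have a" calprotectin decline. Recruited 61, evaluable 58.

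**Assumptions, not in the document.** The stopping shares, and in steps 3 to 5 that every patient lost is a non-responder. Response is read at Week 26, as in the objective and the hypotheses.

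**1. The plan's own figure.** A likelihood-ratio test for one binary predictor, with the 40% taken at the mean of the predictor, needs 59.4 patients, so 60 against the stated 58. If 40% is the overall response rate, the same method needs 63.9. For exclusions, 58/0.95 = 61.05 and 58 × 1.05 = 60.9. The stated figures reproduce to within about two patients and are not in dispute.

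**2. True response by group.** Let p1 be response with a decline and p0 without. Solve 0.8·p1 + 0.2·p0 = 0.40 with p1/(1−p1) = 10·p0/(1−p0). This gives p0 = 8.4% and p1 = 47.9%. Check: 0.8 × 0.479 + 0.2 × 0.084 = 0.40.

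**3. Equal loss of non-responders in both groups.** With overall loss L, the share of non-responders lost is s = L/0.60. Complete-case response is p* = p / [p + (1−p)(1−s)]. For L = 20%, s = 1/3 and p1* = 0.479/(0.479 + 0.521 × 0.667) = 0.58.

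Power is that of a noncentral chi-square test on 1 degree of freedom with noncentrality n·2[H(q) − w0·H(q0) − w1·H(q1)]. Here H(p) = −p·ln p − (1−p)·ln(1−p), q is overall response, and w0, w1 and q0, q1 are the observed group shares and response rates.

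| Overall loss | Evaluable of 61 | No decline | Decline | Overall response | OR | Power |
|---|---|---|---|---|---|---|
| 0% | 61 | 8.4% | 47.9% | 40.0% | 10 | 78% |
| 5% | 58.0 | 9.1% | 50.1% | 42.1% | 10 | 77% |
| 20% | 48.8 | 12.1% | 58.0% | 50.0% | 10 | 72% |
| 30% | 42.7 | 15.5% | 64.8% | 57.1% | 10 | 67% |

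The no-loss baseline is 78%, not 80%, because 40% is taken here as the overall response rate.

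**4. Unequal loss of non-responders.** If shares s0 (no decline) and s1 (decline) are lost, the observed OR is 10 × (1−s0)/(1−s1).
- 60% and 30%: 10 × 0.4/0.7 = 5.7, power about 41%.
- 30% and 50%: 10 × 0.7/0.5 = 14, power about 84%.

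**5. The 5% allowance.** It covers 61 − 58 = 3 patients. With 60% non-response there are 0.6 × 61 = 36.6 non-responders. The allowance is used up if 3/36.6 = 8%, about one in twelve, stop.

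**6. Dependence on the direction of loss.** If a share r of responders also stops, p* = p(1−r) / [p(1−r) + (1−p)(1−s)].
- 20% of each stop: 8.4% and 47.9%, no bias.
- 30% of non-responders and 10% of responders stop: 10.6% and 54.2%, upward.
- 10% of non-responders and 30% of responders stop: 6.7% and 41.7%, downward.

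**The case against.** **The bias is conditional.** A reader might infer that the probabilities are certain to be too high. The document does not support that: the direction depends on who stops, as step 6 shows. The Background makes upward bias the likely direction but gives no rate. This objection stands.

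**At the planned loss the effect is small.** With 5% lost, the decline group moves from 48% to 50% and power from 78% to 77%. That stands too. The larger figures need loss beyond the allowance. A reader might infer that the 5% is contradicted, but it is only unsupported, since no discontinuation figure is given to set against it.

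**An intention-to-treat set with missing outcomes is not a logical contradiction.** One section says who belongs to the set, another how missing values are handled. This is fair, but the two cannot both take effect in a model that needs a Week 26 outcome.

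**The target may be response on treatment.** The Analysis section speaks of response during long-term golimumab, which allows that reading. The intention-to-treat statement and the stated purpose of identifying non-responders early point the other way.

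**The SAP may settle it.** It is not shown and could classify stoppers. The article, however, rules out imputation without exception, and the Study Population section refers to the SAP only for per-protocol exclusions.

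**The odds ratio.** A reader might infer that physicians act on Week 6 results and that the odds ratio is therefore diluted. No section says that they do, and unequal loss can raise the odds ratio as well as lower it.

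**Conclusion.** The concern holds in conditional form. Under the stated rules, a patient who stops golimumab before Week 26 drops out of the primary model, and the document's own account makes these patients likely to be mainly non-responders. If non-responders stop more often than responders given the Week 6 predictors, the predicted probabilities, which are the purpose of the study, are too high.

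The size cannot be fixed from the document. Under the planning assumptions, with loss confined to non-responders and equal across groups, the decline group is overstated by about 2 points at 5% loss, 10 at 20% and 17 at 30%. Loss of power is modest under equal loss. The test of the calprotectin coefficient is biased only if the selective loss differs between predictor groups, and the direction of that cannot be stated in advance.

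**What to change.** - In the primary analysis, count a patient who terminates golimumab before Week 26 for lack of effect as a Week 26 non-responder by outcome definition. This is not imputation. Count stops for intolerance the same way, or vary their handling in a sensitivity analysis.
- Keep the complete-case analysis as a sensitivity analysis, and add multiple imputation for stops for other reasons as another.
- Reconcile the Analysis, Study Population and End of Patient Participation sections on how stoppers count, and restate what the 5% exclusion covers.

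In the equal-loss cases above, where every stopper is a non-responder, counting them so returns 8.4% and 47.9%, 40% overall.

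**Cost.** Wording, and a less favourable response rate. The reason for stopping must also be recorded. The Schedule of Visits does not list it, and enrollment began in October 2014, so it may have to be collected retrospectively for patients already enrolled. The rule needs no extra patients. The only analysis is at study end and enrollment was still open at submission, so the rule could be fixed before the data are analysed.

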### Outcomes

#### Primary

The primary outcome is the prediction of clinical response in Week 26 based on a 50% reduction in fecal calprotectin and a positive golimumab trough level of >2.5 μg/ml in Week 6.

Our definition of a clinical response is a reduction in the partial Mayo score by 2 points between baseline and Week 6, or a partial Mayo score of ≤1 in Week 6.

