#### Hypotheses

The following two-tailed test problem is used for the primary outcome:

Hypothesis 0: beta1=0 versus Hypothesis 1: beta1≠0, where beta1 is the coefficient of the logistic regression model, and null hypothesis: H0. There is no correlation between a significant reduction in fecal calprotectin of 50% from baseline in Week 6 and clinical response to therapy with golimumab in Week 26.

Therefore, our research hypothesis, H1, is that there is a correlation between a significant reduction in fecal calprotectin of 50% from baseline in Week 6 and clinical response to therapy with golimumab in Week 26.

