### Study-Specific Interventions

No medical interventions are carried out in the course of the study other than those required by standard medical procedure. When taking routine blood samples, golimumab serum levels and ATG levels should also be monitored if possible. Only the natural progress of the disease in UC patients is monitored and evaluated.

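### The stated primary predictor pairs calprotectin with golimumab trough, but the hypothesis and the 80% power cover binary calprotectin alone

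*Protocol article*

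**What the plan says.** The protocol article describes the primary predictor in four places.

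- **Abstract (Methods) and Outcomes, Primary.** The outcome is "prediction of clinical response in Week 26 based on a 50% reduction in fecal calprotectin and a positive golimumab trough level", with the trough cut at more than 2.5 μg/ml in Week 6. The opening aim of the Analysis section repeats this pair.
- **Statistics, Analysis.** The section refers the primary outcome to the test in the Hypotheses section and states "The test is carried out with a power of 80% and a two-tailed significance level of alpha=.05". It then gives the model: "Analysis is carried out with a logistic regression model based on the percentage change of fecal calprotectin and golimumab trough levels". That sentence mentions neither the 50% nor the 2.5 μg/ml cut.
- **Statistics, Hypotheses.** The null is beta1=0, "where beta1 is the coefficient of the logistic regression model". In words: "There is no correlation between a significant reduction in fecal calprotectin of 50% from baseline in Week 6 and clinical response" in Week 26. Neither the null nor the alternative mentions trough.
- **Sample Size, Rationale and Calculation.** "It is therefore assumed for sample size calculation that 80% of the patients will have a" decline in calprotectin. With 40% response and an odds ratio (OR) of 10, this gives 58 evaluable patients. Trough has no prevalence, effect size or correlation in the calculation.

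On collection, Study-Specific Interventions says "golimumab serum levels and ATG levels should also be monitored if possible", whereas Schedule of Visits lists trough as measured in Weeks 2 and 6. The Analysis section says that missing values are not imputed.

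**The concern.** These are different models. A coefficient for a calprotectin fall on its own, the same coefficient adjusted for trough, and a coefficient for meeting both cuts answer different questions and have different power. The 80% stated beside the two-marker model was calculated for a one-marker model.

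The interpretation is also at stake. The study is meant to produce an algorithm, and its stated outcome is a two-marker rule. Rejecting beta1=0 as hypothesised would support an association between calprotectin and response. It would say nothing about whether trough adds information, yet the outcome wording would let the result be read as support for the pair.

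**Working it through.** **1. Reproduce the plan's sample size with one binary calprotectin predictor.**

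Inputs from the article: two-sided alpha 0.05, power 80%, prevalence of decline 0.8, response 0.40, OR 10. The SAS procedure is not named. I used the likelihood-ratio chi-square (1 df) for logistic regression, taking the response rate as the probability at the predictor mean.

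- Slope: ln 10 = 2.303. Intercept: ln(0.4/0.6) − 0.8 × 2.303 = −0.405 − 1.842 = −2.248.
- Response without decline: 1/(1 + e^2.248) = 0.096. With decline: 1/(1 + e^−0.055) = 0.514.
- Divergence from 0.40, p ln(p/0.4) + (1 − p) ln((1 − p)/0.6): 0.2344 and 0.0264.
- Noncentrality per patient: 2 × (0.2 × 0.2344 + 0.8 × 0.0264) = 0.1359.
- Noncentrality needed for 80% power: 7.849. N = 7.849/0.1359 = 57.74, so **58**. Power at 58 is **80.2%**.

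The same formula for all nine scenarios:

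| Response | OR 10 | OR 20 | OR 30 |
|---|---|---|---|
| 40% | 57.74 → 58 | 39.77 → 40 | 33.64 → 34 |
| 50% | 49.39 → 50 | 33.96 → 34 | 28.85 → 29 |
| 60% | 44.33 → 45 | 30.04 → 31 | 25.47 → 26 |

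Every evaluable N in Table 3 is matched. The powered model is therefore the one in the Hypotheses section, with calprotectin as the only predictor.

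**2. Add trough as a second binary predictor (simulation).**

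Taken from the article: N=58, 40% overall response, 80% with decline, OR 10 (now the trough-adjusted OR). Assumed: trough positive in 50%, and the associations below. The test is the likelihood-ratio test of the calprotectin coefficient.

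| Calprotectin–trough OR / trough–response OR (assumed) | Power at N=58 |
|---|---|
| 1/1 (trough unrelated to either) | about 82% |
| 3/3 | about 74% |
| 6/3 | about 69% |
| 10/5 | about 60% |

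Repeat runs agree within about two percentage points. Read the rows against the 82% in the first row, not against 80.2%, because the simulation and the formula are different methods.

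A cruder check divides N by (1 − R²), with R² between calprotectin and trough assumed. 57.74/0.9 = 64.2, so 65; 57.74/0.8 = 72.2, so 73; 57.74/0.7 = 82.5, so 83. Power at 58 is then 75.9%, 70.9% and 65.1%.

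**3. Use one composite predictor (both cuts met).**

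The formula is as in step 1, with 40% response; prevalence and OR are assumed.

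| Prevalence of composite | Power at 58, OR 10 | Power at 58, OR 4 |
|---|---|---|
| 70% | 92.7% | 59.8% |
| 50% | 98.0% | 71.2% |
| 20% | 89.3% | 53.9% |

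**4. Read percentage change as continuous.**

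An OR of 10 for decline versus no decline does not carry over to a slope. With an assumed OR per standard deviation, before adjustment for trough, N = 7.849/(0.4 × 0.6 × (ln OR)²):

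- OR 1.5: 7.849/(0.24 × 0.1644) = 198.9, so 199; power at 58 is 32.7%.
- OR 2.0: 7.849/(0.24 × 0.4805) = 68.1, so 69; power 73.4%.
- OR 2.5: 7.849/(0.24 × 0.8396) = 38.95, so 39; power 92.8%.

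The stated 80% is tied to the model in step 1. The article gives no inputs that would fix power for the models in steps 2 to 4.

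**The case against.** The strongest reply is that the primary test is written down. The Analysis section sends the primary outcome to the Hypotheses section, which names a 50% calprotectin reduction, and the sample size is computed for exactly that. This stands. A reader might infer that the trial has no fixed primary test or no valid power figure; the article does not support that. Hypothesis and sample size agree with each other. They disagree with the outcome definition and the model.

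Four further inferences also go beyond the article.

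- **That calprotectin is entered as a continuous variable.** The model sentence does not say so. The same section opens with both cuts, so the sentence may only name the source variables. The coding is ambiguous; the presence of trough is not.
- **That the study is underpowered.** Power under the other versions can also exceed 80%, as step 3 shows. The falls in step 2 depend on assumed associations. The Discussion does assert that detectable drug levels go with response, but gives no size.
- **That many trough values will be missing.** One section makes sampling conditional, while Schedule of Visits lists Week 6 trough as measured. A model with trough may lose patients, but the documents give no rate, so no power figure can be attached.
- **That the analyst will choose the model after seeing the data.** A statistical analysis plan is cited but not shown, and it may fix the coding and covariates.

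The unseen plan does not remove the point, however. The article states conflicting versions, and any analysis plan would have to override one of them.

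**Conclusion.** The contradiction stands. The outcome, the aim and the model include golimumab trough; the hypothesis and the sample size do not. The 80% power at 58 evaluable patients is correct for a single binary calprotectin predictor and is established for no other version.

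With trough in the model, power for beta1 runs from about 82% down to about 60% over the associations tried, assuming an adjusted OR of 10 and trough positive in 50%. For a composite it runs from 53.9% to 98.0% over the prevalences and ORs shown. These ranges show that power is undetermined; they do not predict a shortfall.

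Whatever the power, a significant beta1 as hypothesised would not validate the two-marker rule. Because this concerns which model carries the primary test, it should be settled before analysis.

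**What to change.** Name one confirmatory test: logistic regression of Week 26 response on the binary 50% calprotectin reduction at Week 6, as the sole predictor. This matches the Hypotheses and Sample Size sections and leaves N=58 unchanged. Reword the Abstract, the primary outcome, and the aim and model sentences of the Analysis section to agree with it. Add trough above 2.5 μg/ml as a pre-specified secondary step that asks what it contributes beyond calprotectin. If calprotectin change is also analysed as a continuous variable, the log ratio of Week 6 to baseline is an option, not a requirement.

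If the sponsor prefers to keep trough in the primary test, state a hypothesis that includes it, say how both markers are coded, and restate the power for that model with its assumed trough prevalence and associations. In either case, reconcile the two statements on whether trough is measured routinely or only where feasible.

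The recommended route costs wording in the protocol and the analysis plan and no additional patients. Its downside is that trough has no confirmatory status, which the hypotheses never gave it. The alternative may require a larger sample.

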#### Secondary

In addition to the primary study goal, the following secondary outcomes are analyzed:

1. At which point in time is a 50% reduction in fecal calprotectin a reliable predictor of response?

2. How strong is the correlation between antibody towards golimumab (ATG) level and fecal calprotectin level?

3. How strong is the correlation between ATG and the partial Mayo score?

4. How strong is the correlation between golimumab trough level and fecal calprotectin?

5. How strong is the correlation between golimumab trough level and the partial Mayo score?

6. Do the following parameters exert any influence on clinical response?

      a) C-reactive protein (CRP)

      b) white blood cells (WBC) count

      c) hemoglobin

      d) platelet count

      e) ferritin

7. Frequency of adverse reactions

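### The final algorithm may take in any Week 6 parameter found relevant in the same 58 patients, a number sized for one coefficient; unless corrected, its accuracy and probabilities would be over-optimistic

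*Protocol article*

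**What the plan says.** Under Study Objective, the product of the study is an algorithm that gives a patient's probability of clinical response in Week 26 from Week 6 data.

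The Analysis section describes two steps. The first is a logistic regression on the percentage change in calprotectin and the trough level. In the second, "secondary parameters (eg, ATGs, CRP, WBC) are also analyzed to identify further correlations between the data of Week 6" and Week 26 outcome, and the declared purpose is to "take into account all relevant parameters in the final version of the algorithm". The list is open-ended. Item 6 of the Secondary outcomes asks "Do the following parameters exert any influence on clinical response" and lists CRP, WBC, hemoglobin, platelets and ferritin.

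The sample size serves a narrower question. Under Hypotheses the test concerns beta1 only, "where beta1 is the coefficient of the logistic regression model". The Analysis section adds: "The test is carried out with a power of 80% and a two-tailed significance level of alpha=.05". The Calculation section says that "a worst case scenario with a response rate of 40% and an OR of 10 is used as a basis for sample size", and concludes: "A total of 58 evaluable subjects are therefore necessary for the trial, thus 61 patients must be recruited".

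The same Analysis section calls the secondary outcomes explorative, plans one data analysis at study end, and does not impute missing data.

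**The concern.** Testing one coefficient and building a probability algorithm need different amounts of information. The number of patients was set for the first task, while the headline deliverable is the second. As the text reads, the same patients help decide which parameters are relevant, supply the fitted coefficients, and are the only patients in whom performance can be judged. With few responders per candidate, chance patterns then enter the algorithm. Discrimination looks better than it is, and predicted probabilities lie too close to 0 and 1.

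This matters because the Discussion (Rationale for the Trial) expects the algorithm to help prescribers separate responders from non-responders and act on the result. Probabilities that are too extreme mislead most in exactly that use.

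**Working it through.** **Inputs from the article.** Two-sided alpha 0.05 and power 80% (Analysis); one tested coefficient (Hypotheses); the assumption that "80% of the patients will have a" calprotectin decline (Rationale); response 40%, odds ratio 10, 58 evaluable (Calculation).

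**1. The plan's own figure.** Take 40% as the response probability at the mean of the predictor.
- Intercept: ln(0.4/0.6) − 0.8 × ln 10 = −0.405 − 1.842 = −2.247.
- Response is then 0.096 without decline and 0.514 with decline.
- The likelihood-ratio power calculation (noncentral chi-square, 1 df) gives N = 60, against 58 stated. The same method comes close to the stated number in 8 of the 9 rows of Table 3.
- If 40% is instead the overall response rate, the method gives 64.

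So 58 is about right for its stated purpose, one coefficient, under the first reading.

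**2. Candidates.** The Analysis section names calprotectin, trough, ATG, CRP and WBC (five). The Secondary outcomes add hemoglobin, platelets and ferritin (eight in all), before any interaction or other time point.

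**3. Responders per candidate.** 0.40 × 58 = 23.2, so about 23.
- One tested coefficient: 23/1 = 23.
- Two prespecified predictors: 23/2 = 11.5.
- The five named in Analysis: 23/5 = 4.6.
- All eight: 23/8 = 2.9.

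Under the first reading in step 1, overall response is 0.2 × 0.096 + 0.8 × 0.514 = 0.43, or about 25 responders. At 50% response there are 29, and 29/8 = 3.6. At 60% the smaller class is again about 23. Study-Specific Interventions has trough and ATG measured only if possible, and nothing is imputed, so a multivariable fit may use fewer than 58 patients.

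**4. Expected shrinkage.** The formula is n = p / [(S − 1) ln(1 − R²/S)], where p is the number of candidates, S the expected shrinkage and R² the Cox–Snell value. R² is not in the article and is varied here. Example for p = 8, S = 0.9, R² = 0.15: 8 / (0.1 × 0.1823) = 439.

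| Assumed R² | N for S = 0.9, p = 8 | S at n = 58, p = 8 | N for S = 0.9, p = 2 | S at n = 58, p = 2 |
|---|---|---|---|---|
| 0.15 | 439 | 0.56 | 110 | 0.83 |
| 0.20 | 319 | 0.64 | 80 | 0.87 |
| 0.30 | 198 | 0.74 | 50 | 0.91 |
| 0.40 | 137 | 0.80 | 35 | 0.94 |

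**5. Simulation.** n = 58, 40% response, binary calprotectin decline with odds ratio 10. The other predictors are assumed null to moderate (for example a log odds ratio of 0 or 0.3 per SD). Optimism is apparent AUC minus AUC in new patients.

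| How the model is built | AUC optimism | Median calibration slope (ideal 1) |
|---|---|---|
| All eight fitted | about 0.12–0.17 | 0.25–0.40 |
| Parameters selected by P value | about 0.04–0.13 | 0.30–0.59 |
| Two prespecified predictors only | about 0.01–0.05 | 0.66–0.84 |

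With all eight fitted, apparent AUC is 0.78–0.83 against 0.62–0.70 in new patients. The P-value row combines backward selection from all eight (P < .05 or P < .2) with selection at P < .05 that always keeps the two prespecified predictors. The latter gives the milder end: optimism about 0.04–0.10, slope 0.43–0.59.

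**The case against.** The strongest reply is that this is a condensed article that refers to a separate SAP, which is not shown. A reader might infer that no shrinkage or internal validation is planned. The article does not say so; it neither plans nor excludes them, and such detail commonly sits in the SAP. That part of the reply stands.

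Three further readings also go too far:
- A reader might infer that parameters are to be selected by P value. The article gives no threshold and no selection rule. Its remark on P values concerns how exploratory secondary results are interpreted. P-value selection in the working is therefore an assumption.
- A reader might infer that all eight parameters enter. Only those found relevant would, so the all-eight results are the unfavourable end. A version that also treats trough as pure noise sits badly with the article's expectation, in the Discussion, that trough is associated with response.
- A reader might infer that 58 is wrong. For the beta1 test it is close to reproducible, and that test is unaffected here. The primary model is already confined to two predictors, for which optimism is much smaller.

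What the reply does not remove is in the article itself: an open list of parameters may enter the final algorithm, at a sample size set for one coefficient. Validation specified in the SAP would measure the optimism; it would not make 58 patients enough for eight candidates.

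**Conclusion.** The concern holds in a limited form. Followed as written, the Analysis section leads to a data-driven algorithm from at least eight named candidates with about 2.9 responders each in the planning scenario. Unless corrected, its apparent accuracy and probabilities would be over-optimistic. The size depends on how the model is built: AUC optimism runs from about 0.04–0.13 with selection to 0.12–0.17 with all eight, against 0.01–0.05 for the two prespecified predictors. A calibration slope of 0.25–0.40 means that predicted log odds are spread 2.5 to 4 times too widely (1/0.40 to 1/0.25).

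These figures rest on the article's 40% response and odds ratio of 10, and on assumed strengths for the other predictors, which the article does not give. The direction is the same at every strength tried. This should be changed, but it does not threaten the primary test.

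**What to change.** In the Analysis section:
1. Define the primary algorithm in advance as the two-predictor model already named there, calprotectin change and trough level.
2. List the further candidates, and call any extended algorithm exploratory. Fit it as one penalised logistic model (ridge or lasso).
3. Repeat the whole building process, including any selection, in bootstrap resamples. Report optimism-corrected AUC and calibration slope, for the two-predictor model as well, since its slope also falls short of 1.
4. Describe the result as a development model that needs external validation, and carry that wording into the Conclusions.

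If the SAP already contains steps 2 and 3, a sentence in the protocol pointing to it is enough for those. The cost is some analyst time and a lower reported accuracy. No new data are needed, and neither the sample size nor the beta1 test changes.
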